## Abstract

**Introduction:**

Telmisartan, an angiotensin receptor blocker, has beneficial effects on insulin resistance and cardiovascular health in non-HIV populations. This trial will evaluate whether telmisartan can reduce insulin resistance in HIV-positive individuals on combination antiretroviral therapy.

**Methods and analysis:**

This is a phase II, multicentre, randomised, open-labelled, dose-ranging trial of telmisartan in 336 HIV-positive individuals over a period of 48 weeks. The trial will use an adaptive design to inform the optimal dose of telmisartan. Patients will be randomised initially 1:1:1:1 to receive one of the three doses of telmisartan (20, 40 and 80 mg) or no intervention (control). An interim analysis will be performed when half of the planned maximum of 336 patients have been followed up for at least 24 weeks. The second stage of the study will depend on the results of interim analysis. The primary outcome measure is a reduction in insulin resistance (as measured by Homeostatic Model Assessment—Insulin Resistance (HOMA-IR)) in telmisartan treated arm(s) after 24 weeks of treatment in comparison with the non-intervention arm. The secondary outcome measures include changes in lipid profile; body fat redistribution (as measured by MRI); plasma and urinary levels of various biomarkers of cardiometabolic and renal health at 12, 24 and 48 weeks. Serious adverse events will be compared between different telmisartan treated dose arm(s) and the control arm.

**Ethics and dissemination:**

The study, this protocol and related documents have been approved by the National Research Ethics Service Committee North West—Liverpool Central (Ref: 12/NW/0214). On successful completion, study data will be shared with academic collaborators. The findings from TAILoR will be disseminated through peer-reviewed publications, at scientific conferences, the media and through patient and public involvement.

**Trial registration numbers:**

04196/0024/001-0001; EUDRACT: 2012-000935-18; ISRCTN: 51069819.

Strengths and limitations of this studyThis clinical trial will evaluate whether telmisartan can reduce insulin resistance in HIV-positive individuals on combination antiretroviral therapy; this may lead to the repositioning of telmisartan to treat metabolic disease.The trial will use an adaptive design to inform the optimal dose of telmisartan for reduction of insulin resistance. This design also allows stopping of the trial midway if none of the doses show a statistically significant effect after the interim analysis, thereby reducing the duration of trial and related costs.The trial is assessing a surrogate marker (insulin resistance) as an outcome measure in this trial. Despite the fact that there is a good relationship between insulin resistance and cardiovascular health, this represents a limitation of the trial.

## Background and rationale

Combination antiretroviral therapy (cART) is the mainstay for treatment of HIV and has dramatically improved the morbidity and mortality associated with HIV, turning it into a chronic disease. However, cART, together with the virus itself, can result in various metabolic complications, including metabolic syndrome, type 2 diabetes (T2DM) and an increased risk of cardiovascular disease (CVD).^1^ These metabolic complications associated with cART also occur with HIV lipodystrophy (also known as the fat redistribution syndrome), a clustering of morphological and metabolic abnormalities comprising peripheral fat loss (lipoatrophy), visceral lipid hypertrophy, insulin resistance and dyslipidaemia,^2^ which also increases the risk of CVD.^3^

The prevalence of metabolic syndrome is high in cART treated HIV-infected patients (ranges from 11.2–45.4% in different HIV populations);^4^ the HIV DAD cohort (n=33 347) found the prevalence of metabolic syndrome to increase from 19.4% to 41.6% over a 6-year period with patients having metabolic syndrome showing a fourfold increase in the incidence of T2DM and a twofold to threefold increased risk of developing CVD.^5^ These results have been confirmed by the Multicenter AIDS Cohort Study (n=1278)^6^ and a more recent analysis of the DAD cohort.^7^ Cumulative exposure to cART also results in an increased risk of myocardial infarction with both protease inhibitors^8^ (PIs) and nucleoside reverse transcriptase inhibitors^9^ (NRTIs), as well as in intima-media thickness and an increase in the prevalence of carotid lesions.^10^

Insulin resistance, a key feature of HIV lipodystrophy and metabolic syndrome, has been described as central to cardiometabolic disease and is considered to be an important link between features of metabolic syndrome, obesity, dyslipidaemia, T2DM and CVD.^11^ In vitro studies^12^ and single drug studies in healthy individuals^13^ and HIV-infected patients^14^
^15^ have shown that PIs and NRTIs cause insulin resistance. The prevalence of insulin resistance in cART-treated HIV-infected patients ranges from 10 to 37%,^14–16^ indicating a significant role for cART in its development. Several mechanisms have been suggested to be responsible for cART-induced insulin resistance; these include cART-induced inhibition of adipocyte differentiation,^17^ increased secretion of adipokines such as interleukin 6 (IL-6) and tumour necrosis factor α (TNF-α),^18^ and impairment of the insulin signalling pathway.^12^

Clinical intervention to arrest or reverse cART-associated insulin resistance has been suggested as a strategy to reduce the incidence of T2DM and CVD in HIV-positive patients. Insulin sensitisers such as thiazolidinediones and metformin have been trialled but results from randomised clinical trials in HIV patients have shown mixed results.^19^
^20^ Moreover, the associated adverse effects may limit their use in HIV-infected patients.^21^
^22^ Therefore, there is a need for novel clinical interventions with proven safety profile that can reduce cART-induced insulin resistance in HIV-infected individuals.

Some angiotensin receptor blockers (ARBs) have a beneficial effect on insulin resistance and T2DM, owing to their action on the renin-angiotensin system and partial agonist activity at PPARγ, an important regulator of adipocyte function. Telmisartan shows maximal potency on PPARγ when compared to other ARBs and has been reported to reduce insulin resistance in several in vitro*,*^23^
^24^ animal^25^
^26^ and clinical studies.^27–30^ Telmisartan also improves adiponectin levels, an important metabolic marker of insulin resistance and atherosclerotic disease, lipid control, and has favourable effects on fasting serum insulin and high sensitivity C reactive protein^27^ (high-sensitivity C reactive protein (hs-CRP); a marker of CVD). Telmisartan has also been shown to reduce visceral, but not subcutaneous, fat accumulation in patients with metabolic syndrome.^31^
^32^ Importantly, telmisartan already has a license for cardiovascular protection in a broad group of at-risk patients (ONTARGET trial; 120 000 patient-years of follow-up).^33^

In contrast to the non-HIV population, the effect of telmisartan on insulin resistance in cART-treated HIV-positive patients has not been assessed. Using in vitro adipocyte models, we ([name], unpublished) and others^34^ have shown that telmisartan partially reverses the antiadipogenic effects of antiretrovirals. Our trial has therefore been designed to address this. Furthermore, although the dose-response relationship of telmisartan in hypertension is well known, whether this would also be similar in reducing insulin resistance is unclear. Our in vitro study in fact suggested that there might be a non-monotone (bell shaped) relationship of telmisartan on markers of adipocyte health. We have therefore utilised an adaptive trial design during the initial stage of the study to carefully assess the dose–response relationship of telmisartan in vivo.

## Objectives

The primary objective of the trial is to determine the effect of telmisartan on insulin resistance in HIV-positive individuals on cART using Homeostatic Model Assessment—Insulin Resistance (HOMA-IR). HOMA-IR is a measurable, validated surrogate marker of insulin resistance.^35^

The secondary objectives include assessing the optimal dose of telmisartan that can significantly reduce insulin resistance, evaluation of tolerability of telmisartan in HIV patients and mechanistic evaluation of the metabolic effects of telmisartan. The mechanistic evaluation of telmisartan will explore longitudinal changes in plasma markers that are important indicators of cardiometabolic health (adiponectin, IL-6, resistin, TNFα, hs-CRP and lipids) at different time points; it will also utilise MRI and ^1^H MR spectroscopy (MRS) to assess the effect of telmisartan on total body fat and intrahepatic and intramyocellular triglyceride content, respectively. The MRI/MRS evaluation will be limited to a subset of participants who are recruited locally.

Telmisartan is known to possess renoprotective effects;^36^
^37^ in addition to the above objectives, the study will also assess its effects on the kidney using urinary markers of renal injury (conventional markers such as creatinine, urea, total protein and novel biomarkers such as KIM-1, NGAL and RBP).

## Trial design

This study is a phase II, multicentre, randomised, open-labelled, dose-ranging trial of telmisartan in HIV-positive individuals over a period of 48 weeks. The sample size for the study is 336 (see Sample size calculation), but a total of 370 patients will be recruited to participate in this study to account for patient withdrawals (estimated to be 10%).

The optimal dose of telmisartan that elicits the desired response is not known; hence, an adaptive design is utilised for this study. The first stage of the study will be dose-ranging where patients will be randomised 1:1:1:1 to receive one of three doses of telmisartan (20, 40 and 80 mg) or no intervention (control). An interim analysis will be performed when half of the planned maximum of 336 patients have been followed up for at least 24 weeks. The second stage of the study will depend on the results of interim analysis, which could be one of the three outcomes listed below:
One or more active dose groups are substantially more effective than control; this will lead to a stopping of the study and the corresponding dose(s) will be taken directly into phase III.No dose shows sufficient promise at the interim analysis; this will also lead to a stopping of the study.At least one of the doses shows some improvement over control at interim analysis; this will lead to a second stage where that/these dose(s) will be followed up along with the control for a further 24 weeks (total: 48 weeks). Additional patients will also be recruited to these dose(s) and control. If at the final analysis a large enough reduction in 24 week HOMA-IR score is found, the corresponding active dose will be recommended for phase III.

In the telmisartan 40 and 80 mg arms, dose titration will be undertaken over 2−4 weeks in order to step up to the allocated dose (as per the Summary of Product Characteristics; SPC), or else the maximum tolerated dose if the target is not achieved. All assessments will be carried out at baseline and at weeks 12, 24 and 48 post-treatment with telmisartan, as well as in the control arm. For those who participate in the MRI/MRS substudy, assessment will be at baseline and 24 weeks. The study flow diagram is given in figure 1.

**Figure 1 BMJOPEN2015009566F1:**
[figure not shown]
Flow Diagram for TAILoR Trial. The trial will be conducted in two stages. Stage 1 of the study is dose-ranging and patients will be randomised 1:1:1:1 to receive one of three doses of telmisartan or no intervention (control). An interim analysis will be performed when half of the planned maximum of 336 patients have been followed up for at least 24 weeks. Stage II of the study will depend on the results of interim analysis, which could be one of the three outcomes shown in the figure. All assessments will be carried out at baseline and at weeks 12, 24 and 48 post-treatment with telmisartan, as well as in the control arm. For those who participate in the MRI/MRS substudy, assessment will be at baseline and 24 weeks. TEL: Telmisartan.

The Clinical Trials Research Centre (CTRC), University of Liverpool, is the coordinating centre for this study (http://www.liv.ac.uk/translational-medicine/research/ctrc/about/).

## Patient recruitment

### Identification of eligible patients

Patients who are eligible for inclusion into the trial will be identified and recruited through HIV specialty centres located in the UK that have agreed to participate in the study. These HIV specialty centres are part of the secondary care system and are mostly based in an urban setting. Participants will be identified by the clinical team at each centre via a search of the patient database(s) either electronically or manually or a clinic list review to find potentially eligible patients. The inclusion and exclusion criteria are detailed in box 1.
Box 1Inclusion and exclusion criteria*Inclusion criteria*
Adult (age 18 or above) HIV-positive individuals receiving antiretroviral therapy for at least 6 months. The antiretroviral therapy may contain:
A boosted protease inhibitor (LPV/r, ATV/r, DRV/r, FAPV/r, SQV/r)and/or efavirenz, rilpivirine or etravirineThe backbone can be based on N(t)RTI, raltegravir or maraviroc. Patients on protease inhibitor monotherapy will be included if they meet other criteria. Patients on nevirapine or dolutegravir regimens, without concomitant boosted PIs, should not be included. Additionally, patients on elvitegravir, which is administered in combination with cobicistat (as Stribild), should not be recruited.Ability to give informed consentWillingness to comply with all study requirements*Exclusion criteria*
Pre-existing diagnosis of type 1 or 2 diabetes (Fasting glucose >7.2 mmol/L or HbA1c≥6.5% [48 mmol/mol] or abnormal OGTT or random plasma glucose≥11 mmol/L)Patients known to have consistently low blood pressure (pre-existing hypotension; A reading below a threshold of 100/60 mm Hg on three separate occasions)Patients with renal disease (eGFR<60 in the 6 months preceding randomisation)Patients with known untreated renal artery stenosisPatients with cholestasis, biliary obstructive disorders or severe hepatic impairment.Patients with evidence of an active, chronic hepatitis C infectionPatients who are on unboosted ATVPatients who are on/ have been on hormone therapy, anabolics and insulin sensitisers within 6 months preceding randomisation. Patients on hormonal contraception are eligible.Patients who are already on/ have been on other ARBs, ACE inhibitors or direct renin inhibitors within 4 weeks preceding randomisation.Those with suspected poor compliancePregnant or lactating womenWomen of childbearing age unless using reliable contraception, for example, coil, barrier method, hormonal contraceptive that does not interact with their antiretroviral therapyCo-enrolment in other drug trialsPatients who have participated in a trial of an IMP likely to influence insulin sensitivity, plasma insulin, glucose levels or plasma lipid levels within 6 months preceding randomisation.For the subcohort of patients undergoing MRI/MRS, normal MR exclusion criteria will apply (See Body fat distribution substudy).ARB, angiotensin receptor blockers; ATV, atazanavir; DRV, darunavir; eGFR, estimated glomerular filtration rate; FAPV, fosamprenavir; HbA1c, glycated haemoglobin; IMP, investigational medicinal product; LPV/r, lopinavir/ritonavir; N(t)RTI, nucleoside (nucleotide) reverse transcriptase inhibitors; OGTT, oral glucose tolerance test; PI, protease inhibitor; SQV, saquinavir.

### Consent procedure

At the routine clinic visit, eligible patients are informed of the study by a member of the clinical team or research staff. A Patient Information Sheet and instructions on how to proceed if they are interested in taking part will be provided by the research nurse. All patients will be provided with a full explanation of the trial and given sufficient time to consider their decision before obtaining informed written consent. In consenting to the trial, patients are consenting to trial treatment, follow-up and data collection. Patients are free to withdraw consent at any time without providing a reason. Follow-up of these patients will be continued through the trial research nurses and the lead investigator at each centre unless the participant explicitly also withdraws consent for follow-up.

### Baseline assessments

Once informed consent has been obtained from the patient, they will be booked in for a baseline assessment visit within 30 days of giving consent. The patient will be advised to arrive fasting when reporting for the baseline assessment. The research team will conduct the baseline assessments and complete the eligibility and baseline case report form (CRF) during the baseline assessment visit. The baseline assessments include fulfilment of eligibility criteria; recording demographic details; full medical and drug history; body weight and vital signs; and waist/thigh circumference. A urine pregnancy test is offered for females of childbearing potential since telmisartan is not recommended during the first trimester of pregnancy and is contraindicated during the second and third trimesters of pregnancy due to its teratogenic potential. However, a refusal to undertake a pregnancy test will not preclude trial entry. Blood samples (for plasma, serum and DNA) and urine will also be collected from each patient at the time of baseline screening. Table 1 details the schedule of study assessments conducted.

**Table 1 BMJOPEN2015009566TB1:** Schedule of study procedures

			T+2 week	T+4 weeks				
Time	Pre T0 At each recruitment site	T0 Randomisation/baseline*	Dose titration—40/80 mg arms (dose given 40 mg)	Dose titration for 80 mg arm (dose given 80 mg)	T+12 weeks Follow-up	T+24 weeks Follow-up	T+48 weeks End of treatment	Premature withdrawal of consent
Database search to identify potential participants or clinic list review	Х							
Information sheet provided to patient	X							
Signed informed consent		Х						
Assessment of eligibility criteria by a medically qualified person		Х						
Review of medical history (including collection of most recent blood test results for urea and electrolytes, eGFR, liver function, diabetes screening, etc		Х†					X	Х
Review of concomitant medications		Х	Х	Х	Х	Х	Х	Х
Urine pregnancy test		Х			X	X		
Randomisation		Х						
Study intervention		Х	Х	Х	Х	Х		
Compliance with study intervention—patient diaries and pill counting			X	X	Х	Х	Х	
Physical examination—complete		Х						
Physical examination—symptom-directed			Х	Х	Х	Х	X	Х
Height		Х						
Weight		Х			Х	Х	Х	Х
Waist/thigh circumference		Х			Х	Х	Х	Х
Heart rate, blood pressure		Х	Х	Х	Х	Х	Х	Х
Collection of 3 fasting blood samples for bioanalysis		Х			Х	Х	Х	Х
Collection of urine sample		X			X	X	X	X
Assessment of adverse events			Х	Х	Х	Х	Х	Х
Consent for substudy		X						
MRI/MRS scan for substudy		X				X		

(X)—As indicated/appropriate.

*Baseline assessment and randomisation visit should be within 30 days of the patient giving consent.

†Liver function and diabetes screening result only to be collected at baseline.

eGFR, estimated glomerular filtration rate; MRS, MR spectroscopy.

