## Randomisation

Participants will be randomised to receive telmisartan 20, 40, 80 or control (no intervention) in a 1:1:1:1 ratio once (A) eligibility criteria have been fulfilled; (B) fully informed written consent has been obtained; and (C) baseline assessments have been completed. Participants will be randomised using a bespoke secure (24 h) web based randomisation programme controlled centrally by the CTRC, University of Liverpool. For each recruiting centre, randomisation will be stratified by ethnicity (African-American and non-African-American) where ethnicity is determined by self-categorisation using the NHS ethnicity codes. Centres will be provided with emergency back-up randomisation envelopes to be used in the event of a system failure or when a system failure cannot be resolved in a reasonable time frame. Patients may only be randomised into the study by an authorised member of staff at the study site as detailed on the delegation log. Participants may only be randomised into the study once.

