## Trial interventions

Telmisartan is an angiotensin receptor antagonist indicated for clinical use as an antihypertensive agent. It is also used to reduce cardiovascular events in patients who are at risk. However, the current trial uses telmisartan outside its licensed indications.

At the onset of the trial, telmisartan was under patent (Boehringer Ingelheim GmBH; Micardis); however, during the course of the trial, the patent expired and several manufacturers started marketing generic telmisartan, which was then also used in the trial, but the trial will continue to use Micardis SPC as the reference SPC. Telmisartan used in this trial is sourced via usual local NHS procurement arrangements.

Telmisartan tablets are available in 20, 40 or 80 mg doses and therefore fit in with the dose range to be used in the trial prior to interim analysis. In most cases, the participant is provided their required dose in one tablet. Telmisartan tablets are for once-daily oral administration and should be taken with liquid, with or without food. The CRFs will be used to record which brand has been dispensed to the participant. Telmisartan is stored as per the manufacturer's SPC.

For each randomised patient, treatment is for a maximum period of 48 weeks. The principal investigator or delegated other will issue a prescription based on the patient's randomisation status and the trial treatment can start immediately after randomisation. For the three treatment arms, treatments will be dispensed at the appropriate doses at baseline, at 12 weeks and then at 24 weeks, unless interruption or discontinuation is warranted. Wherever titration of dose is required, the treatment starts with 20 mg and is then titrated upwards over a period of 2 weeks (for a 40 mg dose) or 4 weeks (for an 80 mg dose). At 48 weeks, administration of trial treatments will be stopped and any unused medications will be returned to pharmacy for disposal via their local procedures. There is a 2 week attendance window on either side of each of the follow-up visits and a 4 day window on either side of the titration visits.

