Since the results of the interim analysis decide the design of stage II of the trial, those patients who are on a dose that is not taken forward to stage II will be asked to stop taking the medication completely. These patients will continue to be monitored for any adverse events for a period of 7 days (washout period for telmisartan) after which they will no longer be part of the trial and will return to routine care. For those who are on trial arms whose dose(s) are taken forward to stage II, they will be asked to continue on the same dose for a further 24 weeks. Since treatment is not stopped between stages I and II, some participants may receive up to a maximum of 48 weeks trial treatment before the results of the interim analysis are known. For patients recruited after the results of interim analysis are known, they will be randomised equally to the non-intervention (control) arm and the remaining telmisartan dose arm(s).

Dose modifications will be allowed in those who are randomised to a particular dose arm but do not tolerate that dose. The patient will be allowed to continue on the nearest dose tolerated. Those who show adverse effects as a result of the trial intervention or due to the HIV therapy may be withdrawn from the trial treatment. The decision to interrupt or discontinue trial therapy is at the discretion of the treating physician using their informed clinical opinion. Any changes will be documented in the CRF along with the justification for those changes. Patients who withdraw from study treatment will be asked to allow continuation of scheduled evaluations, complete an end-of-study evaluation if appropriate and be given appropriate care under medical supervision until the symptoms of any adverse event resolve or the patient's condition becomes stable. Follow-up of these patients will be continued through the trial research nurses and the lead investigator at each centre unless the participant explicitly also withdraws consent for follow-up. Data up to the time of withdrawal will be included in the analyses unless the patient explicitly states that this is not their wish.

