### Reporting of pregnancy

Female study participants of childbearing potential will be offered a pregnancy test as part of the trial screening process and at weeks 12 and 24. Any pregnancy which occurs during the study will be reported as an SAE to the CTRC within 24 h of the site becoming aware of its occurrence and the participant will be instructed immediately to stop taking study drugs. All pregnancies that occur during treatment need to be followed up until after the outcome. The investigator will discuss the risks of continuing with the pregnancy and the possible effect to the fetus with the participant.

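### Refusing the baseline pregnancy test does not bar randomisation, so telmisartan can start in a woman whose pregnancy exclusion no test has verified

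*Protocol article*

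**What the plan says.** All references are to the Protocol article.

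- **Box 1, exclusion criteria.** Women who are pregnant or breastfeeding are excluded. Women of childbearing age are also excluded unless they use reliable contraception; a barrier method is among the accepted examples.
- **Baseline assessments.** A urine pregnancy test is offered to women of childbearing potential because telmisartan is "not recommended during the first trimester of pregnancy and is contraindicated during the second and third trimesters of pregnancy". The next sentence reads: "However, a refusal to undertake a pregnancy test will not preclude trial entry". The same section says that "urine will also be collected from each patient at the time of baseline screening".
- **Table 1.** The pregnancy test is scheduled at T0, week 12 and week 24. The T0 column also contains "Assessment of eligibility criteria by a medically qualified person".
- **Randomisation.** Allocation may take place once "eligibility criteria have been fulfilled", consent is in place and baseline assessments are done.
- **Trial interventions.** After allocation, "the trial treatment can start immediately after randomisation".
- **Reporting of pregnancy.** Women of childbearing potential "will be offered a pregnancy test as part of the trial screening process", and again at weeks 12 and 24. If a pregnancy occurs, study drug is stopped immediately and the pregnancy is reported as a serious adverse event within 24 hours.

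**The concern.** The article sets an exclusion, explains why it matters for this drug, and then lets a participant waive the only procedure it names for testing it. For a woman who declines, the clinician must declare the pregnancy criterion met without a test result, and no substitute check is described.

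What is at stake is participant safety. A site following the text exactly can start telmisartan, used here outside its licence, in a woman who is already pregnant without knowing or disclosing it. There is little to set against that risk: the drug is an adjunct given to study a surrogate marker, and the Ethical considerations section says control of HIV does not depend on it. A woman who is not enrolled forgoes no HIV treatment.

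**Working it through.** The article gives no figure on this point to reproduce. The check is first a reading of the sections against each other, then simple arithmetic on how long the gap can last.

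**1. Does anything verify non-pregnancy in a woman who declines?**

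| Safeguard | Where | Shows she is not pregnant at randomisation? |
|---|---|---|
| Reliable contraception required | Box 1 | No. It lowers the probability; no minimum prior duration of use is stated |
| Eligibility assessed by a clinician | Table 1 | No. No means of excluding pregnancy is named apart from the test she declined |
| Medical history and complete physical examination | Baseline assessments, Table 1 | No. An early pregnancy she does not know of or report can be missed |
| Drug stopped if pregnancy is found | Reporting of pregnancy | No. It acts only after exposure |

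Nothing in the article makes the test compulsory or supplies another check.

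**2. Chance that she receives telmisartan**

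- Stage 1, 1:1:1:1 across three doses and control: 3/4 = 75%.
- After the interim analysis, equal allocation to control and the k remaining doses: k/(k + 1), which is 1/2 = 50%, 2/3 = 67% and 3/4 = 75% for k = 1, 2, 3.

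These are allocation odds, not rates of harm.

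**3. Time to the next scheduled test offer**

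The next offer is at week 12, with a 2-week window either side: 12 − 2 = 10 to 12 + 2 = 14 weeks after treatment can start. That offer can also be declined.

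**4. Gestation at that point**

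Assumptions, not from the article: a baseline urine test detects pregnancy from about 4–5 weeks' gestation, and the second trimester begins at 13–14 weeks.

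- Lower end: 4 + 10 = 14 weeks.
- Upper end: 5 + 14 = 19 weeks.

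So the earliest pregnancy that the baseline test could have found would be at 14–19 weeks by the next offer, unless recognised sooner by other means. A pregnancy further advanced at baseline would be later still. The lower end only just reaches the assumed second-trimester boundary; the rest of the range lies beyond it.

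**5. Participants whom a change could still reach**

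The recruitment target is 370 (Trial design) and 293 had been recruited (Time frame and trial status): 370 − 293 = 77. This is an upper bound. It includes men and women who would accept the test, and it assumes the full target is recruited.

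**The case against.** The strongest reply is that this is a deliberate, disclosed choice. The drug risk and the refusal rule stand in adjacent sentences, an ethics committee approved the protocol, and the trial holds a Clinical Trial Authorisation. Refusal waives only the test: pregnant women remain excluded and reliable contraception is a firm entry criterion. The women at risk are those of childbearing potential who use contraception, are nonetheless pregnant, do not know or say so, and decline the test. That group is likely to be very small.

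The 10–14 week interval is also a worst case. It counts test offers only. The 40 and 80 mg arms have a titration visit at week 2, and the 80 mg arm another at week 4, each with a symptom-directed examination and adverse event review. Finally, this is a condensed article; the full protocol or patient information sheet might say how a refusal is handled.

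Much of this stands as a limit on size. The number affected is probably small, and the titration visits give some chance of earlier recognition in two of the three active arms. It does not remove the point. Those visits include no pregnancy test, and the 20 mg arm has no scheduled visit before week 12. Approval does not supply the missing check, and the Ethical considerations section discusses contraception without addressing entry after a refused test. The refusal rule is stated outright, so it is not a detail left to a fuller document.

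**Conclusion.** The concern holds. As written, a woman can be randomised and start telmisartan without any test having verified that she meets the pregnancy exclusion. The existing safeguards reduce the likelihood of exposure but do not establish her status on the day.

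The size can be bounded only in part. The allocation odds and the 10–14 week interval follow from the article. The 14–19 week gestation rests on the two stated assumptions. The number of women affected cannot be derived, because neither the refusal rate nor the number of women of childbearing potential is given.

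This is a safety and eligibility point that should be corrected. Sample size, type I error, power and the primary analysis are not affected.

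**What to change.** Replace the refusal sentence in Baseline assessments with a rule along these lines: every woman of childbearing potential must have a negative urine pregnancy test before randomisation, and a woman who declines the test is not randomised. Change the screening wording in Reporting of pregnancy from offered to required. The offers at weeks 12 and 24 can stay; this change addresses only pregnancies already present at entry.

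The cost is an amendment to one sentence plus the matching screening wording. No extra visit or sample is needed, because the test is already scheduled at T0 and urine is already collected from every patient at baseline. The downside is that a few women who decline testing will not be enrolled. At the article's date the change could reach at most 77 further participants, and in practice only the women of childbearing potential among them.
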